### Interim analyses {21b}

Although an interim analysis will not be conducted, the trial should be terminated if there is clear evidence that serious adverse events (SAEs) are associated with the intervention.

### Methods for additional analyses (e.g. subgroup analyses) {20b}

Multivariate logistic regression will be used to conduct exploratory analyses. Based on insomnia duration, insomnia can be categorized into acute insomnia (lasting up to three months) and chronic insomnia (lasting at least 3 months) [39]. A subgroup analysis will be conducted based on the duration of insomnia after stroke.

### Methods in analysis to handle protocol non-adherence and any statistical methods to handle missing data {20c}

The evaluation of the outcomes will be based on an intention-to-treat analysis (ITT). Before statistical analysis of the data, the missing data mechanism will be examined, and the missing data pattern will be investigated. Multiple imputation (MI) is a principled missing data method that provides valid statistical inferences under missing at random conditions [40]. Considering 20% missing data, at least five imputations will be necessary [41]. We will select the preferred imputation method based on the missing data pattern [41].

### Plans to give access to the full protocol, participant-level data, and statistical code {31c}

The datasets generated and analysed during the study will be available from the corresponding author on reasonable request.

## Oversight and monitoring

### Composition of the coordinating centre and trial steering committee {5d}

The coordinating group is composed of the research coordinator and nurses. Nurses are responsible for communicating with patients who are interested in the recruitment advertisement and performing the phone call consultation and WeChat visit of the participants. The research coordinator will help the principal investigator obtain the contact details of potential participants and communicate with patient advisers who provide their experiences as patients with post-stroke insomnia to the design and details of this study. The steering committee (SC) is composed of the subject leader and the project manager. The SC will be responsible for the surveillance of the quality control and the progress of the study. The SC will appoint inspectors as a monitor group to oversee this study in accordance with the Good Clinical Practice guidelines. The monitor group will conduct daily supervision activities and then will write the inspection report, which will mainly include the quality of the CRF form, researchers’ compliance with the protocol, and recruitment processing of patients to the steering committee every week. The SC will have the authority to allow modification of the plan.

### Composition of the data monitoring committee, its role, and reporting structure {21a}

The administrators at the Medical College of China Three Gorges University will be responsible for monitoring data management as an independent third party. The administrators will write the data monitoring report, which will mainly include the accuracy of entries and the data entry staff’s knowledge of various standards, to the SC every week.

### Adverse event reporting and harms {22}

When adverse events (AEs) occur, it will be necessary to record the name of the AE, the beginning and end times of the AE, the outcomes of the AE, the severity of the AE, the treatments related to the AE, causality, and the application of combined drugs. The researchers will analyse causality based on the following five criteria: (1) Is there a reasonable time sequence between the intervention and AE? (2) Is the AE consistent with the type of AEs known to be associated with the intervention? (3) Did the AE disappear or decrease after discontinuation of the intervention? (4) Does the same AE appear when the patient receives the same intervention? (5) Can the AE be explained by a combination of medications or by the patient’s disease progression?

AEs will include nausea, tiredness, dizziness, syncope, palpitations, hepatic dysfunction, and kidney dysfunction. SAE harms include death, life-threatening, hospital treatments, and permanent disability.

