## Objectives {7}

Although some studies have shown acupuncture combined with SZRD is more beneficial for insomnia [20, 21], whether EA combined with SZRD is more effective and safer for insomnia after stroke needs more clinical and experimental evidence. Therefore, we will combine EA with SZRD as a clinical treatment method for patients with post-stroke insomnia. We aim to assess whether the combination therapies are more effective and safer for insomnia after stroke than independent usage of the two treatments and to preliminarily uncover the possible mechanisms underlying the effect of the combination therapy.

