## Trial design {8}

The study is designed as a 12-week, single-centre, randomized, single-blind, controlled trial. Study participants will be included according to the inclusion and exclusion criteria. Before starting the treatment, all eligible patients will undergo a standard neuroimaging examination (brain magnetic resonance imaging and functional magnetic resonance imaging), a baseline evaluation of sleep quality, neurological deficits, anxiety and depression, and measurement of nocturnal melatonin concentrations. Then, subjects will be equally randomized into four groups: the EA group, SZRD group, EA & SZRD group, and sham group. Patients in the EA group and sham group will receive EA stimulation or sham EA every other day for 4 consecutive weeks for a total of 14 sessions. Patients in the SZRD group will only take SZRD granules orally twice a day for 4 consecutive weeks. Patients in the EA & SZRD group will be administrated SZRD granules orally twice a day for 4 consecutive weeks, combined with EA stimulation every other day for 4 consecutive weeks, for a total of 14 sessions. Assessments will be carried out at baseline (before treatment), during the 2nd and 4th weeks of the intervention, and at the 8th and 12th weeks of follow-up.

The trial will be performed according to the principles of the Declaration of Helsinki (Fortaleza version, 2013), the Consolidated Standards of Reporting Trials [22], the Standards for Reporting Interventions in Clinical Trials of Acupuncture [23], and Recommendations for Intervention Trials (SPIRIT) Checklist.

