## Data collection and management

### Plans for assessment and collection of outcomes {18a}

All data will be documented in detail in the CRF after face-to-face visits. The same researcher will be responsible for the examination of each patient at each assessment. Baseline measurements, medical history, demographics, and previous medications will be collected at the first visit. The primary and secondary outcomes will be assessed at baseline (before treatment) and during the 2nd and 4th weeks of the intervention, as well as at the 8th and 12th weeks of follow-up. Safety assessments will be evaluated at baseline and during the 4th week of the intervention.

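### Symptomatic adverse events are recorded as they occur while in-person contact differs by arm, so that part of the safety comparison of EA & SZRD with SZRD alone is open to unequal detection

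*Protocol article*

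**What the plan says.** Objectives {7} makes safety a comparative aim: "We aim to assess whether the combination therapies are more effective and safer for insomnia after stroke than independent usage of the two treatments". EA & SZRD versus SZRD is one of the two comparisons this implies; EA & SZRD versus EA is the other.

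Adverse event reporting and harms {22} gives the recording rule: "When adverse events (AEs) occur, it will be necessary to record the name of the AE", followed by the other details to be noted and the causality criteria. It then names the events: "AEs will include nausea, tiredness, dizziness, syncope, palpitations, hepatic dysfunction, and kidney dysfunction".

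Contact during treatment differs by arm. Trial design {8} says of the herbal arm: "Patients in the SZRD group will only take SZRD granules orally twice a day for 4 consecutive weeks". The combination arm takes the granules "combined with EA stimulation every other day for 4 consecutive weeks, for a total of 14 sessions", and the EA and sham arms have the same 14 sessions (also Table 1).

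Some contact is common to all arms. Plans for assessment and collection of outcomes {18a} states: "The primary and secondary outcomes will be assessed at baseline (before treatment) and during the 2nd and 4th weeks of the intervention", with further assessments at weeks 8 and 12, and has data entered after face-to-face visits. Calls and WeChat messages are planned without distinction by arm, for adherence ({11c}) and retention ({18b}). Section {5d} gives nurses the task of phone and WeChat contact. Safety assessments lists laboratory tests and ECG at baseline and week 4 in every arm.

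Who will be blinded {17a} bars acupuncturists and data collection staff from exchanging information and restricts their communication with patients.

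**The concern.** Five of the seven named AE types are symptoms. They enter the data only if the patient mentions them or someone sees them. The scheduled safety tests do not ask about them. Brief, mild events such as tiredness or dizziness could come up at a session held every other day. An SZRD patient would have to remember them until a visit or raise them on a call made for another purpose.

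The contact difference arises after allocation, as part of the treatment itself, so randomisation does not balance it. Patients in both arms of this comparison also know what they receive ({17a}). A difference in symptomatic AE counts between EA & SZRD and SZRD could then reflect opportunity to report rather than tolerability, and a real difference could be hidden.

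**Working it through.** **Contacts (from the protocol).** Every other day over 28 days gives 28 / 2 = 14 sessions, which reproduces the stated 14. The shared on-treatment assessments are weeks 2 and 4.

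| | EA, sham, EA & SZRD | SZRD |
|---|---|---|
| Treatment sessions | 14 | 0 |
| Shared visits, weeks 2 and 4 | 2 | 2 |
| In person during treatment | 16 | 2 |
| Adding weeks 8 and 12 | 18 | 4 |

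These are appointments. The protocol does not say that each one is an occasion on which AEs are recorded.

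**Which parts of safety are exposed.**
- Nausea, tiredness, dizziness, syncope, palpitations: depend on report or observation, so exposed.
- Hepatic and kidney dysfunction, ECG findings: tested on the same schedule in every arm, so not exposed.
- EA & SZRD versus EA: 14 sessions in both arms, so not exposed to this imbalance.

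**Illustrative size.** The protocol gives no AE risk and no capture probability, so all of these are assumptions. Observed risk = true risk × capture. Take a true risk of 20% in both arms and 60 patients per arm (Sample size {14}).
- EA & SZRD, capture 90%: 0.20 × 0.90 = 0.18, or 10.8 patients expected.
- SZRD, capture 75%: 0.20 × 0.75 = 0.15, or 9.0 patients; risk ratio 0.18 / 0.15 = 1.2.
- SZRD, capture 60%: 0.20 × 0.60 = 0.12, or 7.2 patients; risk ratio 0.18 / 0.12 = 1.5.

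The chance that a two-sided Fisher exact test at 0.05 shows the combination as worse when there is no true difference, by exact enumeration with 90% capture in the combination arm:

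| Capture in SZRD arm | Observed risks | Combination falsely worse |
|---|---|---|
| 90% | 18% v 18% | 1.4% |
| 75% | 18% v 15% | 3.8% |
| 70% | 18% v 14% | 5.3% |
| 60% | 18% v 12% | 9.6% |
| 50% | 18% v 10% | 16.6% |

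**Masking.** If the true risks were 15% (combination) and 25% (SZRD), capture of 90% and 54% would give 0.15 × 0.90 = 0.135 and 0.25 × 0.54 = 0.135. The advantage would disappear.

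**Direction.** The figures above assume that sessions raise capture. If patients mention events to the acupuncturist and, because of the bar on exchange in {17a}, these do not reach the CRF, capture could be lower in the combination arm. Swapping the assumed values, 60% for the combination and 75% for SZRD, gives 0.12 / 0.15 = 0.8, in favour of the combination.

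**The case against.** The strongest reply is that this is a condensed article. Section {22} says what is recorded about an AE, not how it is elicited, and nowhere says that patients are not asked at visits. A standard prompt may already be on the CRF or in the full protocol. That limits how firmly the point can be put, but it does not remove it: the comparative aim, the event-triggered rule and the unequal contact are all stated, and nothing stated equalises detection. If a common prompt exists, half of the fix is already in place and what remains is to base the comparison on it.

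A reader might infer that the SZRD arm is unobserved. It is not: it has the same face-to-face visits, and calls and messages reach every arm. These narrow the gap by an unknown amount, but their stated purposes do not include asking about AEs. Data management {19} has administrators check that all AEs are in the CRFs. That is a check on the forms and is unlikely to find a symptom nobody reported.

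A reader might also infer that the whole safety comparison is biased, and biased against the combination. The documents support neither. Laboratory and ECG safety is symmetric, and {17a} leaves it unclear whether sessions feed the CRF at all, so neither the presence nor the direction of bias is established.

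It is also fair to say that the effect is modest on moderate assumptions: about 2 to 4 patients of 60 at capture of 60–75% against 90%.

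**Conclusion.** The concern holds in limited form. For symptomatic AEs, the comparison of EA & SZRD with SZRD alone is open to detection bias, because recording is event-triggered and in-person contact during treatment is 16 against 2. The bias is a possibility the plan leaves open, not a demonstrated fact. Its direction depends on whether events noted at sessions reach the CRF.

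On an assumed 20% true risk and capture of 90% against 60–75%, the spurious risk ratio is 1.2–1.5, and a false finding that the combination is worse occurs in 3.8–9.6% of trials, against 1.4% with equal capture. These figures rest on capture rates that the protocol does not give and serve only to show scale. The point is worth correcting because the affected comparison is one of the two named in the safety objective and the correction is cheap.

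**What to change.** Use one identical symptomatic-AE checklist in all four arms at the existing week 2, 4, 8 and 12 visits, covering the time since the previous visit. Have the patient complete it, since answers given aloud to blinded data collection staff could reveal the arm. Keep the form free of treatment-specific wording.

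Make these answers the primary basis for between-arm comparison of symptomatic AEs. Report all AEs as well, including those noted only at sessions, separately by source (checklist, session, call or message, laboratory or ECG).

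The cost is one extra form at visits already planned and a sentence or two in the analysis section. There are small downsides. The checklist relies on recall, over two weeks during treatment and four weeks during follow-up, and events noted only at a session do not enter the primary AE comparison, though they are still reported.

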### Frequency and plans for auditing trial conduct {23}

Our trial will be audited every 6 months by qualified clinical trial experts, and the review process will be independent of researchers and sponsors.

### Plans for communicating important protocol amendments to relevant parties (e.g. trial participants, ethical committees) {25}

If there is any change to eligibility criteria, outcomes, or analyses, a new version of the protocol will be submitted to the Medical Ethics Committee of College of Traditional Chinese Medicine, China Three Gorges University & Yichang Hospital of Traditional Chinese Medicine, for approval.

## Dissemination plans {31a}

The results of the study will be presented in the form of publications or conference reports.

## Discussion

A stroke occurs when a blood vessel that carries oxygen and nutrients to the brain is either blocked by a clot or bursts (or ruptures), which frequently leads to long-term deficits in physical and cognitive functions in patients [42]. Insomnia is one of the most common complications in stroke patients [43]. Although the exact pathophysiology between insomnia and stroke remains complicated, a basic consensus has been reached that the pathophysiological mechanisms linking insomnia with worse stroke outcomes may be relevant to sympathetic overactivation, hypoxaemia, oxidative stress, and inflammatory reactions [44]. Some studies have provided evidence that insomnia patients show inferior motor function and other worse stroke recovery, and it is believed that healthy sleep plays an important role in the restoration and compensation of neurological functions associated with stroke [45–47]. Ameliorating insomnia during any phase of stroke is positive for short- and long-term recovery [47].

SZRD, one of the most widely used CHM formulas, has been utilized for insomnia for thousands of years in China [19]. A network analysis revealed that the five herbs in SZRD may play different roles in a coordinated manner to exert a range of sedative and hypnotic actions via GABAergic and serotonergic systems [48]. GABAergic activity not only improves sleep but also promotes sleep-related learning and memory processes, which are potentially relevant to neurorehabilitation after stroke [49]. In addition, it has been found that SZRD is beneficial for balancing the nervous system, regulating blood sugar and blood pressure, normalizing the hormone system, and improving the inflammatory response [50].

EA has been used in the treatment of stroke for decades [51]. Recently, it has also been widely utilized as a clinical treatment for insomnia [52]. An evidence-based review showed that EA significantly alleviates pathological damage and promotes post-stroke functional recovery via neurogenesis and astrogliosis [53]. Accumulating data have documented that EA may effectively work by a variety of neurotransmitters, such as adenosine, GABA, galanin, and glutamate, which are related to improving sleep quality [54]. Some clinical RCTs have indicated that EA or EA combined with other therapies is effective for the treatment of insomnia [55, 56].

Therefore, we propose to conduct a clinical RCT on EA plus SZRD for the treatment of post-stroke insomnia. We designed a randomized, four-group, and single-blinded clinical trial with a 4-week treatment period and a 12-week follow-up period. Based on TCM theory and previous studies, *Shenmen* (HT7), *Sanyinjiao* (SP6), *Baihui* (GV20), and *Shenting* (GV24) are the most frequently selected acupoints for the treatment of post-stroke insomnia, and local acupoint stimulation can improve the curative effect when combined with distal acupoints [57, 58]. We also emphasize the experience of the “*de qi*” sensation during the intervention. There have been differences in efficacy between low-frequency and high-frequency electrical stimulation in EA therapy [59, 60]. Accumulating data have shown that low-frequency EA is effective for complications related to stroke, such as insomnia, epilepsy, and pseudobulbar palsy [61–63]. We selected a 10-Hz frequency of EA to treat insomnia after stroke in this trial. Preliminary analyses have indicated that different types of sham acupuncture may have different effect sizes, and a meta-analysis showed that sham devices may have minimum non-specific effects [64, 65]. We chose to apply a sham device in the sham group to ensure the precision of the results.

Non-invasive neuroimaging technology is the most commonly recommended diagnostic tool in stroke [66]. Technologies such as fMRI open a window for the study of insomnia after stroke. Some researchers have found that patients with primary insomnia have abnormal brain metabolism and connectivity related to particular brain regions, such as the prefrontal cortex, insular cortex, amygdala, precuneus, and caudate [67, 68]. Thus, we can utilize fMRI to assess aspects of treatment-induced changes in resting-state brain metabolism and elucidate the possible underlying mechanisms of these therapies in this protocol.

Melatonin is a hormone secreted by the pineal body, with peak secretion at night [69]. Some researchers have found that abnormal secretion of melatonin is potentially related to insomnia in stroke patients [70, 71]. A preliminary report revealed that acupuncture increased nocturnal melatonin secretion and reduced insomnia and anxiety [72]. We will detect the nocturnal melatonin concentrations in patients with post-stroke insomnia to investigate whether EA plus SZRD can also play a beneficial role by increasing nocturnal melatonin secretion and reducing insomnia.

We hope to elucidate the possible underlying mechanisms of this combination therapy by using MRI and melatonin detection. However, our study has some limitations. One limitation is the use of self-rating scales, which might affect the evaluation of the severity of the insomnia disorder. However, we will attempt to decrease the subjective factors by PSG. Another limitation is that the trial will be performed in a single-blind manner, and it will be conducted in only one medical centre. These limitations may weaken the generalizability of the study. A large sample, multicentre, study using objective measures to assess the efficacy of EA plus SZRD treatment should be conducted in a future study.

## Trial status

Recruitment began in April 2020 and the approximate date when recruitment will be completed is January 2022. Protocol version 2.0 was approved on January 16, 2020.

## Abbreviations

EA: Electroacupuncture
SZRD: Suanzaoren decoction
TCM: Traditional Chinese medicine
CHM: Chinese herb medication
PSG: Polysomnography
PSQI: Pittsburgh Sleep Quality Index
ISI: Insomnia Severity Index
HADS: Hospital Anxiety and Depression Scale
NIHSS: National Institutes of Health Stroke Scale
MRI: Brain magnetic resonance imaging
fMRI: The functional magnetic resonance imaging
MLT: Nocturnal concentration of melatonin
RCT: Randomized controlled trial
CRF: Case report form
